## Methods and analysis

### Study design and setting

We will conduct a longitudinal, prospective, cohort study among adult sarcoma patients, newly diagnosed in one of the participating study centres (five centres in the Netherlands: Radboud University Medical Centre Nijmegen, Erasmus Medical Centre Rotterdam, University Medical Centre Leiden, University Medical Centre Groningen, Netherlands Cancer Institute Amsterdam; three centres in the UK: The Royal Marsden London, Christie Manchester, Royal Orthopaedic Hospital Birmingham, all NHS Foundation Trusts). The study started recruitment at the first centre in the Netherlands in February 2018 and in the UK in October 2018 and is currently recruiting.

After informed consent, patients are being asked to complete questionnaires at five points in time: the first at baseline, preferably before start of treatment or within 4 weeks thereafter, and at 3, 6, 12 and 24 months follow-up (table 1). Baseline questionnaire completion will take about 45 min, follow-up questionnaires will take 20–30 min each.

**Table 1 T1:** Time points and questionnaire items

Item (number of items)	Scale	0 months	3 months	6 months	12 months	24 months
Characteristics						
Sociodemographic (max 20)		X	X	X	X	X
Comorbidity (15)	SCQ	X			X	X
Total interval (max 42)	Own design	X	X	X	X	X
Health literacy (1)	SBSQ	X				
Social support (1)	QLCS	X		X		X
Self-efficacy (10)	GSE	X				
Coping (28)	Brief COPE		X			
Resilience (6)	BRS			X		
Outcomes						
Health-related quality of life (30)	EORTC QLQ-C30 version 3.0	X	X	X	X	X
Quality-adjusted life years (6)	EQ5D5L	X	X	X	X	X
Psychological distress (14)	HADS	X	X	X	X	X
Financial impact (20)	Own design	X	X	X	X	X
Information provision (max 26)	Profiles registry		X			
Quality of care (max 23)	PSQ-18 and 3–5 single items	X	X	X	X	X
Total number of items		194	158	105	113	114

BRS, brief resilience scale; COPE, Coping Orientation to Problems Experienced; EORTC QLQ, European Organisation for Research and Treatment of Cancer Quality of Life Questionnaire; EQ5D5L, European Quality of life 5 Dimensions 5 Levels; GSE, general self-efficacy; HADS, hospital anxiety and depression scale; PSQ, patient satisfaction questionnaire; QLCS, quality of life-cancer survivors; SBSQ, set of brief screening questions; SCQ, self-administered comorbidity questionnaire.

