### Endpoints

The primary endpoint is HRQoL of patients with sarcoma at diagnosis (baseline) as measured with the EORTC QLQ-C30 (global health status). Secondary endpoints are: QALY, psychological distress, stage and tumour size at diagnosis, PFS and OS.

If subgroups are large enough, we will conduct these analyses for different clinically relevant subgroups, such as different histological subtypes, geographical areas, and so on.

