### Sample size calculation

We expect a minimum response rate at baseline of 65%, based on rates in other PROFILES studies.^40^ During follow-up, after completion of the first questionnaire, we expect a response rate of 80%. The definition of a long total interval will follow from our statistical analysis (see below), however, if the analysis does not provide a clear cut-off point, we will use the last quartile to define the population with a long total interval.

Using the EORTC QLQ-C30, differences of at least 10 points have been considered as clinically meaningful.^41^ Based on results from our ongoing PROFILES studies, an SD of about 20 points for each scale can be expected. Using an alpha of 0.05, a power of 0.90 and a long diagnostic interval of 25% in the total group of patients with sarcoma, with the expected drop-out, would require 265 patients.^42^ In order to make country-to-country comparisons, we aim to include 265 Dutch and 265 English patients in a time frame of 18 months with a total follow-up of 24 months.

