Change in HRQoL during the follow-up period of 2 years and factors associated with changes in HRQoL will be analysed using repeated measures mixed models. This will be compared between patients with a short and long total interval, using repeated measures analysis of variance, controlling for relevant patient and tumour characteristics, and the patient’s baseline score. Clinically relevant differences will be assessed using Cocks’ method.^41 42^

Other patient-reported outcomes such as QALYs and psychological distress will be analysed in the same way.

Multivariate analyses will be performed to examine associations between total interval length and (1) QALYs, (2) psychological distress, (3) stage at diagnosis and (4) tumour size. These analyses will be corrected for potential confounders including patient and tumour characteristics and healthcare system.

Both unadjusted and adjusted multivariate Cox proportional hazard regression analyses will be used to examine whether a long total interval is associated with PFS or OS.

PFS is defined as the time interval between diagnosis until clinical or radiological progression, as assessed by the treating consultant. OS is defined as the time from diagnosis until death.

Statistical analyses will be performed using IBM SPSS V.25.0; two-sided p values <0.05 will be considered statistically significant.

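### The short-versus-long comparison over two years is assigned to repeated measures ANOVA controlling for baseline HRQoL, although the mixed model already planned uses incomplete patients and avoids conditioning on a post-exposure outcome

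*Protocol article*

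**What the plan says.** All references are to the protocol article.

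- **Statistical analysis, follow-up.** Consecutive sentences name two methods. First, change over two years and "factors associated with changes in HRQoL will be analysed using repeated measures mixed models". Then the short and long interval groups are compared "using repeated measures analysis of variance, controlling for relevant patient and tumour characteristics, and the patient’s baseline score". QALYs and psychological distress are to be handled likewise.
- **Study design and setting.** Questionnaires are completed at baseline "and at 3, 6, 12 and 24 months follow-up", so there are four follow-up visits.
- **Sample size calculation.** "During follow-up, after completion of the first questionnaire, we expect a response rate of 80" per cent, without saying whether this is per visit or over the whole follow-up. The target is 265 patients in each country.
- **Missing data.** The section deals with missing items. It gives no rule for a whole questionnaire that is not returned.
- **Introduction and Endpoints.** The total interval runs from first symptom to diagnosis. The primary endpoint is global health status on the QLQ-C30 at diagnosis, which is the same score that later serves as the covariate.
- **Statistical analysis, baseline.** The association of interval with baseline HRQoL has its own analysis, and the cut-off for a long interval is to be sought where baseline HRQoL differs.

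**The concern.** There are two separate problems in one sentence.

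First, repeated measures ANOVA in its usual form takes one complete row per patient, so a single missed questionnaire removes the patient from the comparison. In a sarcoma cohort followed for two years, those who return every questionnaire may well be in better health than those who do not. The mixed model in the sentence before has no such requirement.

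Second, the exposure is over by the time the baseline score is taken, and the study expects the exposure to affect that score. Adjusting for it conditions on an outcome of the exposure. The groups are not randomised, and the cut-off rule favours a split at which they differ at baseline. That is the setting in which a baseline-adjusted contrast departs from the difference in change. A reader told that the analysis concerns change could take a non-zero adjusted contrast as evidence that the groups diverge, when they only started apart and stayed apart.

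**Working it through.** **The plan's own figure.** Inputs from the Sample size calculation: difference 10, SD 20, two-sided alpha 0.05, power 0.90, 25% with a long interval (3:1).

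- Smaller group = (1 + 1/3) × (20/10)² × (1.960 + 1.282)² = 56.04, so the unrounded total is 4 × 56.04 = 224.2. Rounded up by group: 57 + 171 = 228.
- Dividing by 0.80 gives 285, not 265. Conversely, 265 × 0.80 = 212 (53 long, 159 short) gives power 0.88, close to the stated 0.90. The stated figure is thus met approximately if 80% of patients supply the data analysed. The point here does not depend on it.

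**Patients left by a complete-row analysis.** Inputs: four follow-up visits and 80% response. The counts take 265 (or 530) as patients with a baseline questionnaire, which is an assumption.

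| Reading of 80% | Share complete | Of 265 | Power for 10 points | Of 530 | Power for 10 points |
|---|---|---|---|---|---|
| Per visit, independent | 0.8⁴ = 0.41 | 109 | 0.62 | 217 | 0.89 |
| All visits completed | 0.80 | 212 | 0.88 | 424 | 0.99 |

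Power is for an unadjusted comparison at a single time (SD 20, 25% long), as a guide to lost precision and not as the power of the longitudinal test. Visit-to-visit dependence in response would put the share between the two rows. Under the first row, 1 − 0.2⁴ = 99.8% of patients have at least one follow-up score and would contribute follow-up data to a mixed model.

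**Selection.** The documents give no drop-out mechanism, so only a range can be shown. Simulations assumed a constant 10-point gap, 530 patients, within-patient correlation 0.55, and drop-out depending on the last observed score. Complete patients then showed a gap of about 9.8, 9.1 or 7.7 points as the assumed log-odds slope rose from 0.25 to 0.5 to 1.0 per SD. The bias is small under weak dependence and material only under strong dependence.

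**Baseline as covariate.** Let the groups differ by D at every visit, with equal variance and the same correlation ρ between any two visits of one patient. The within-group slope of the follow-up mean on baseline is then ρ, so the adjusted group difference is

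D − ρ × D = D × (1 − ρ).

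With D = 10, and ρ assumed because the documents do not give it:

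| ρ | Formula | Simulated adjusted difference | Simulated unadjusted difference | Simulated difference in change |
|---|---|---|---|---|
| 0.3 | 7.0 | 7.1 | 10.1 | 0.1 |
| 0.5 | 5.0 | 5.0 | 10.0 | 0.0 |
| 0.7 | 3.0 | 3.0 | 9.9 | 0.0 |

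(Absolute values; 2,000 runs of 265 patients, 25% long, missing completely at random.) The adjusted figure matches neither the total gap of 10 nor the true difference in change of 0, and it moves with ρ.

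**The case against.** **The wording may be loose.** The second sentence can be read as describing the group contrast within the mixed model just named, with ANOVA as an informal label. A reader might infer that the protocol excludes patients with a missed visit; it nowhere says so. Deletion follows from the classical form of the named procedure. This stands as a limit on the claim, but two different methods remain named for one analysis and need reconciling.

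**The loss may be modest.** A reader might take 109 patients as the sample left. That is the per-country figure under independent 80% response at each visit. The comparison is not restricted to one country, and on the other reading of 80% most patients remain. This also stands, which is why a range is given. Nor do the documents support any single figure for bias from selective drop-out.

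**Baseline adjustment can be legitimate.** It asks whether long-interval patients do worse later than short-interval patients with the same starting score. That is a coherent question, and the baseline effect has its own analysis, so it is too strong to say that the effect is adjusted away: a share of about ρ is removed from this contrast. But the protocol presents the comparison as one of change and does not declare a baseline-conditional target.

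**Stage and tumour size.** One might go on to argue that these should also be left out, as consequences of the interval. The protocol names neither for this model, and its Introduction warns that poor adjustment for tumour aggressiveness may explain earlier null findings. That choice is a genuine trade-off and forms no part of this point.

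**Conclusion.** The point holds for the longitudinal comparison of HRQoL and, by extension, of QALYs and distress, which are secondary endpoints. The primary baseline analysis is unaffected.

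The named ANOVA, in its classical form, would use 41% to 80% of patients; the lower end assumes independent 80% response at each visit. It loses precision and is open to bias of unknown size if drop-out depends on health. Controlling for baseline HRQoL would turn a constant 10-point gap into about 7 to 3 points for an assumed correlation of 0.3 to 0.7, with no true difference in change. Those figures rest on a constant gap and equal correlation between visits. The general conclusion, that the adjusted contrast is neither the total difference nor the difference in change, needs only that the groups differ at baseline and that scores correlate within patients.

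This should be changed because the better method is already in the protocol.

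**What to change.** Make the short-versus-long comparison within the planned mixed model:

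- All five time points, baseline included, as outcomes.
- Fixed effects for interval group, time and their interaction, plus the confounders already planned.
- Report the group difference at each visit and the difference in change, both from this model.
- Remove the baseline score as a covariate. If a baseline-adjusted result is still wanted, label it as a secondary estimate conditional on baseline.
- Apply the same to QALYs and psychological distress.

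The cost is a reworded sentence and slightly more modelling work. The mixed model relies on a missing-at-random assumption for missed questionnaires, which should be stated.

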Possible risk factors for a prolonged total interval could be patient, tumour or healthcare system characteristics. In order to study the latter, it is informative to compare patients from different countries. In both the Netherlands and UK, general practitioners (GPs) have an important role as healthcare gatekeepers. In general, people consult their GP who then decides whether referral is warranted and determines the acuteness and location of the referral. In the UK, privately insured patients can also self-refer to a hospital without seeing a GP. Furthermore, within the UK, a considerable amount of patients with cancer is diagnosed at an emergency department, associated with worse outcomes.^11^ Sarcoma care is formally centralised within the UK, whereas the Netherlands has bone sarcoma centres, and referral to dedicated STS centres is encouraged, but not commissioned. Furthermore, cultural differences may play a role in patient behaviour. Also, longer travel time to a sarcoma centre in the UK compared with the Netherlands may also affect total interval length.

Up to now, only few studies regarding total interval length and clinical outcomes in sarcoma have been published, most were retrospective and included mainly children. Some studies found that a longer total interval worsened OS, while others did not find inferior clinical outcomes.^10^ Researchers have argued that this lack of an association, often referred to as the ‘waiting-time paradox’, may be because the studies have not been able to adequately adjust for the aggressiveness of the cancer tumours. The most significant effect of a long interval for sarcomas seems to be the increasing size of the lesion,^12^ with consequent decreased chance of uncomplicated resection with clear surgical margins, a greater risk of amputation and increased risk of developing metastases.^13^ This may also affect patient-reported outcomes such as HRQoL of patients with sarcoma.

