### Statistical analysis

Descriptive statistics (means, SD, median, range, frequencies) will be used to quantify diagnostic intervals and describe the study population.

HRQoL at baseline will be calculated according to the EORTC scoring manual.^43^ Missing items will be imputed according to these guidelines, after which an available case analysis will be performed.

The relationship between total interval length and HRQoL at baseline will be investigated by plotting HRQoL against total interval length as a continuous variable. Linear regression will be used to assess their association. The time point providing a significant difference in HRQoL will be used as a cut-off point for further analysis. If this does not provide a clear cut-off point, logistic regression will be used to assess an association between baseline HRQoL and total interval grouped into suitable categories, such as quartiles. The last quartile will then be used to define the population with a long interval.

Apart from statistical significance, we will look at clinically relevant differences in HRQoL scores as determined by Cocks *et al.*^42^ A small effect size will then be considered as an appropriate value for a cut-off point.

A series of univariate logistic regression analyses will be conducted to assess the relationship between total interval length (grouped by the cut-off point as defined by the previous analysis) and independent variables, such as patient, tumour and healthcare system risk factors. All factors with p<0.1 will then be used in multiple logistic regression analysis (forced entry method) to investigate whether these factors are independently associated with total interval length.

Apart from total interval length, the association of other patient and tumour characteristics (such as self-efficacy, social support, financial difficulties, histology), and HRQoL at baseline will be investigated using univariate logistic regression analysis. Using the forced entry method, multiple logistic regression analysis will then be performed with all factors with p<0.1 to assess what factors are independently associated with baseline HRQoL.

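### The Cox models for PFS and OS and the short-versus-long comparison of two-year HRQoL dichotomise total interval, which costs information if the effect is graded and cannot show a non-linear relation

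*Protocol article*

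**What the plan says.** All references are to the protocol article.

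- **Aim.** The Abstract and the end of the Introduction set out to determine the association of total interval with HRQoL, stage, tumour size, PFS and OS.
- **Baseline HRQoL (Statistical analysis).** The interval is plotted and regressed as a continuous variable. A cut-off for later analyses is then sought in these data. Failing a clear one: "The last quartile will then be used to define the population with a long interval".
- **Two-year HRQoL (Statistical analysis).** After mixed models for change and its associated factors, the section says: "This will be compared between patients with a short and long total interval". The comparison controls for patient and tumour characteristics and the baseline score.
- **PFS and OS (Statistical analysis).** Unadjusted and adjusted models are planned: "Cox proportional hazard regression analyses will be used to examine whether a long total interval is associated with PFS or OS". No continuous, multi-category or non-linear interval term is stated for these endpoints.
- **Background (Introduction).** Some earlier studies found no link between interval and outcome. The Introduction reports the argument that this missing link, "often referred to as the ‘waiting-time paradox’, may be because the studies have not been able to adequately adjust for the aggressiveness of the cancer".
- **Sample size calculation.** One figure is given, for HRQoL. No event count, hazard ratio or power is given for PFS or OS.

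**The concern.** The aim concerns a graded quantity, but for these outcomes the analysis treats everyone on the same side of one cut as equally exposed. Two things follow.

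First, if risk rises steadily with the interval, the cut discards the variation within each group and the analysis loses precision. The protocol states no power margin for PFS or OS that could absorb this.

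Second, the reference group always contains the shortest intervals, wherever the cut falls. If fast-growing tumours tend to be diagnosed quickly and do badly, risk may be raised at both ends of the interval scale. One long-versus-short hazard ratio cannot separate that pattern from a flat relation. A weak or null result would then leave the ambiguity that the Introduction describes in earlier work.

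**Working it through.** **1. The plan's own figure.** The inputs are in Sample size calculation: "Using an alpha of 0.05, a power of 0.90 and a long diagnostic interval of 25% in the total group of patients with sarcoma"; "differences of at least 10 points have been considered as clinically meaningful"; "an SD of about 20 points for each scale can be expected". Statistical analysis adds "two-sided p values <0.05 will be considered statistically significant".

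- Short group: (1.960 + 1.282)² × 20² × (1 + 3) / 10² = 168.1, so 169. Long group: 169 / 3, so 57. Total: 226 evaluable.
- Dividing by the 80% follow-up response gives 283; dividing by the 65% baseline response gives 348. Neither is the stated 265.

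That mismatch is a separate matter. It concerns HRQoL and does not affect the present point. PFS and OS have no planned figure to reproduce.

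**2. Information kept by a cut.** For a normally distributed exposure with a log-linear effect, cut so that a share p is long, the share of information kept is φ(z)² / [p(1 − p)], where z is the (1 − p) normal quantile. At p = 0.25, z = 0.6745 and φ(z) = 0.3178, so 0.1010 / 0.1875 = 0.539, a loss of 46.1%.

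Power after the cut is Φ[√0.539 × (1.960 + z_power) − 1.960]:

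- from 90%: Φ(0.734 × 3.242 − 1.960) = Φ(0.42) = 66%
- from 80%: Φ(0.734 × 2.802 − 1.960) = Φ(0.10) = 54%

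| Share called long | Information lost | 90% power becomes |
|---|---|---|
| 50% | 36% | 73% |
| 33% | 41% | 70% |
| 25% | 46% | 66% |
| 15% | 57% | 56% |
| 10% | 66% | 47% |

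For uniform, exponential and lognormal exposures cut at the top quartile, the loss ranged from 36% to 56%.

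**3. The same loss in events.** The hazard ratios here are assumptions. For 80% power the continuous analysis needs (1.960 + 0.842)² / (ln HR per SD)² events. The top-quartile analysis needs (1.960 + 0.842)² / [0.1875 × (1.695 × ln HR per SD)²], because the two groups differ by 0.3178 / 0.1875 = 1.695 SD on average.

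- HR 1.3 per SD: 115 versus 212 events
- HR 1.4 per SD: 70 versus 129 events

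**4. What one contrast hides.** Assume, without adjustment, hazards of a, 1, 1 and 1.5 across the interval quartiles. The long-versus-rest ratio is about 1.5 / [(a + 2) / 3]. For a = 1.25, 1.5 and 2.0 this gives 1.38, 1.29 and 1.13, where the ratio against the middle half is 1.5. Simulation gave 1.39, 1.28 and 1.13. The protocol gives no such hazards, so this only illustrates the mechanism.

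**5. Where the bias comes from.** A cohort of 60,000 was simulated with a true log-HR of 0.2 per SD of log interval, an aggressiveness factor that raises the hazard, and a top-quartile cut. Entries are the estimate as a percentage of the true value. The continuous term is linear.

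| Relation of aggressiveness to interval | Continuous, unadjusted | Binary, unadjusted | Continuous, adjusted | Binary, adjusted |
|---|---|---|---|---|
| none | 90 | 94 | 97 | 101 |
| correlation −0.3 | 28 | 27 | 103 | 97 |
| correlation −0.6 | −49 | −46 | 103 | 87 |
| 20% aggressive, short-interval subgroup | 5 | 23 | 102 | 90 |

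Omitting aggressiveness damages both forms about equally, and a linear term fares worse in the last row. Adjusting for it restores most of the effect in both.

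**The case against.** The strongest reply is that the waiting-time paradox is a problem of confounding, and the protocol plans to adjust. Adjusted Cox models are stated, the HRQoL comparison controls for tumour characteristics, and histology, TNM stage and tumour size are collected (Case report forms). The Introduction's remark calls for better adjustment and says nothing about the form of the exposure. This stands. A reader might infer that the split itself causes harm from delay to be understated, but the documents do not support that: in step 5 the shrinkage comes mainly from unadjusted aggressiveness.

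Further points that stand:

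- The 46% is conditional. The first-choice cut-off comes from the data, so its share is unknown. If the true effect is a step at the cut, a linear continuous term loses the 46% instead.
- A reader might infer from step 4 that a model separating the shortest quartile would be much better at detecting harm from long intervals. Part of any such gain would be detection of excess risk at the short end, which is not an effect of delay.
- It would be too strong to say HRQoL over time is analysed only as long versus short. The mixed models for factors associated with change leave the form of the interval unstated.
- PFS and OS are secondary endpoints, and a condensed article may leave knots and reporting percentiles to the full protocol.

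The last point does not dispose of the matter. The long-versus-short wording is a stated choice, and it differs from the continuous treatment of baseline HRQoL in the same section.

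**Conclusion.** The concern holds as a point about efficiency and about what the analysis can show. The stated analyses of PFS and OS, and the short-versus-long comparison of two-year HRQoL, use a dichotomised interval although the aim is the association with total interval.

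Under a roughly log-linear effect of a normally distributed (for example log-scale) exposure, the fallback cut loses about 46% of the information; across cuts with 50% to 10% long, the loss is 36% to 66%. A single contrast cannot display a non-linear relation. Understatement of harm is a possibility where adjustment for aggressiveness is incomplete, as in the unadjusted model; it is not an established consequence of the split. The change is worth making because it is cheap, but the planned analysis is not invalid without it.

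**What to change.** In the Statistical analysis section, for the adjusted Cox models of PFS and OS and for the mixed model of HRQoL over time:

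- Enter log total interval as a restricted cubic spline with 3 or 4 knots at percentiles fixed in advance, or as ordered categories with a middle reference group.
- Include the collected markers of aggressiveness, such as histology, in the same models. Stage and tumour size are themselves listed as outcomes of the interval, so state separately whether they enter.
- Test the overall association and non-linearity. Report hazard ratios or score differences at chosen percentiles, for example the 10th, 75th and 90th, against the median.
- Keep long versus short as a secondary summary.

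The cost is revised wording and a few computed columns; no new data are needed. A spline with 3 or 4 knots uses two or three degrees of freedom instead of one, and the main result becomes a curve rather than one hazard ratio. The spline complements adjustment for confounding and does not replace it: without adjustment it would display a confounded shape, not remove it.

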HRQoL is the patients’ perception of his overall health in relation to physical, psychological and social aspects in life.^14^ Three systematic reviews have been published on HRQoL of patients with sarcoma, however, none of these looked at the association of total interval length and HRQoL.^15–17^ In other cancers and chronic diseases, lengthening of total interval was associated with decreased HRQoL.^18 19^ HRQoL is an interesting outcome parameter for evaluating consequences of long total interval length and provides an insight into the patient’s experience of the consequences of diagnostic delay. In addition to using patient-reported outcomes as a measure for quality of care, HRQoL can be used to conduct cost-utility analysis to estimate the ratio between the cost of a prolonged total interval and the benefit of earlier diagnosis in terms of life-years (quality-adjusted life years (QALY)).

Until now, risk factors for a long total interval in adult sarcoma care as well as its effect on clinical and patient-reported outcomes remain unknown. These need to be studied in well-designed, large, prospective studies in order to prioritise interventions to optimise the total interval. Our study aims to quantify total interval, identify independent variables associated with a long interval (such as demographic and clinical factors) and determine the association between total interval and other dependent variables, such as HRQoL, stage and tumour size at diagnosis, progression-free survival (PFS) and OS (figure 1).

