### Case report forms

CRFs will be completed at five time points during the study. The first will be completed on inclusion, the following time points coincide with the completion of follow-up questionnaires. The last CRF is also the end-of-study CRF, which can be completed before 24 months if a patient withdraws or deceases. The information collected on the CRF will be stored on a secure CRF database using anonymous study numbers. Data collected includes documentation of eligibility criteria, date of diagnosis, tumour characteristics such as histology, tumour, node and metastasis (TNM) stage, tumour size, treatment regiment, re-occurrence of disease or metastases, reason for withdrawal of the study and time of death, if applicable.

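### PFS is defined with progression as its only event, so the planned Cox model analyses time to progression, not progression-free survival

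*Protocol article*

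**What the plan says.** The Statistical analysis section of the protocol article defines the two time-to-event endpoints in consecutive sentences: "PFS is defined as the time interval between diagnosis until clinical or radiological progression, as assessed by the treating consultant", and then "OS is defined as the time from diagnosis until death". Death is an event for OS and is not mentioned for PFS. Both endpoints go into the same analysis, in which unadjusted and adjusted "Cox proportional hazard regression analyses will be used to examine whether a long total interval is associated with PFS or OS".

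The Introduction spells the endpoint out as "progression-free survival (PFS) and OS", and the Endpoints section makes it secondary: "Secondary endpoints are: QALY, psychological distress, stage and tumour size at diagnosis, PFS and OS". The Case report forms section foresees death during follow-up ("The last CRF is also the end-of-study CRF, which can be completed before 24 months if a patient withdraws or deceases") and collects the date, listing "reason for withdrawal of the study and time of death, if applicable" among the recorded items. Recurrence and metastases are recorded there too.

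No section adds death to the PFS event or says how a death without progression is to be handled.

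**The concern.** The label and the definition describe different endpoints. A patient who dies without progression has not survived progression-free, yet under the stated rule that patient contributes no event. This is not a detail left to a fuller document: the article gives a complete event definition, and that definition is of time to progression.

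Two things are at stake. First, the PFS result would not be comparable with studies that count progression or death, although it would carry the same name. Second, the association of a long total interval with PFS is part of the study's third aim. If interval length acts differently on progression and on death without progression, the two definitions give different hazard ratios, and a reader would attribute the progression-only ratio to the wrong endpoint.

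**Working it through.** The plan states no PFS rate, event count, hazard ratio or power, so there is no figure to reproduce. The check is first textual and then illustrative.

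**1. Who counts as an event under the stated rule**

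| Patient's course | PFS as written | Progression or death | OS |
|---|---|---|---|
| Progression, then death | event at progression | event at progression | event at death |
| Progression, alive | event at progression | event at progression | censored |
| Death, no recorded progression | no event; censored at death | event at death | event at death |
| Alive, no progression | censored | censored | censored |

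The definitions differ only in the third row. Censoring at death is not written in the protocol. It follows from fitting a Cox model in which progression is the only event.

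**2. Share of events lost (illustration)**

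Assumed, not in the documents: constant hazards of hp = 0.30 per year for progression and hd = 0.03 to 0.10 per year for death without progression.

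Share of first events that are deaths = hd / (hp + hd)
- Low end: 0.03 / 0.33 = 9%
- High end: 0.10 / 0.40 = 25%

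**3. Effect on the hazard ratio**

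Let s be the share of deaths without progression among first events in the short-interval group, and HRp and HRd the long-versus-short hazard ratios for progression and for death without progression. With constant hazards:

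- progression only: HR = HRp
- progression or death: HR = (1 − s) × HRp + s × HRd

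The two agree only if HRd = HRp or s = 0. With assumed s from 0.05 to 0.30 and HRp = 1.3:

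- HRd = 2.0: 0.95 × 1.3 + 0.05 × 2.0 = 1.34, up to 0.70 × 1.3 + 0.30 × 2.0 = 1.51. The progression-only ratio is the smaller.
- HRd = 1.3: 1.30 throughout. Nothing changes except the number of events.
- HRd = 1.0: 0.95 × 1.3 + 0.05 × 1.0 = 1.29, down to 0.70 × 1.3 + 0.30 × 1.0 = 1.21. The progression-only ratio is the larger.

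The sign of the difference is therefore set by whether HRd is above or below HRp, and the documents give neither.

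**4. Effect on events and power (illustration)**

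From the Sample size calculation section: 265 + 265 = 530 patients, 24 months, and 25% with a long interval (the fallback definition). From the Statistical analysis section: "two-sided p values <0.05 will be considered statistically significant". Assumed: 50% of short-interval patients have progression or death by two years. Power is by Schoenfeld's formula, with z = √(D × 0.25 × 0.75) × ln(HR) − 1.96 for D events. Ranges run from s = 0.05 to s = 0.30.

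| Assumption | Definition | HR | Events | Power |
|---|---|---|---|---|
| HRp 1.3, HRd 1.3 | progression only | 1.30 | 264 to 194 | 45% to 35% |
| | progression or death | 1.30 | 277 | 47% |
| HRp 1.3, HRd 2.0 | progression only | 1.30 | 263 to 191 | 45% to 35% |
| | progression or death | 1.34 to 1.51 | 279 to 285 | 55% to 85% |

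The last pair of rows compares power for two different quantities. Its gain comes from the assumed HRd of 2.0 and is not a property of the study.

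**The case against.** The strongest reply has four parts.

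*A Cox model that censors deaths is legitimate.* It estimates the cause-specific hazard of progression, a reasonable target for a question about association. This stands. The fault is that the quantity is reported under the name of another one; the model itself is sound.

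*The direction of any distortion is unknown.* A reader might infer that censoring deaths pulls the hazard ratio towards no association, since delay is expected to produce larger tumours and more metastases. The documents do not support that. The Introduction also raises the waiting-time paradox: earlier studies may have failed to find an association because they could not adequately adjust for tumour aggressiveness. If aggressive tumours are diagnosed quickly, deaths without recorded progression could cluster in the short-interval group, and leaving them out would raise the ratio for a long interval. This objection stands in full.

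*The size may be small.* Progression may be clinical, so imaging is not required; clinical and survival data come from medical records; recurrence and metastases are on the CRF; and patients too ill for questionnaires are excluded. Each could make death without recorded progression less frequent. This stands as a limit on size, but it does not repair the definition. A reader might also infer that a 24-month PFS percentage would be overstated. The article plans only Cox regression for PFS and no such percentage, so that inference attaches to no stated output.

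*The wording may simply be incomplete.* The article is condensed, and censoring rules commonly sit elsewhere. It is possible that the authors intend to count deaths, and nothing shows a deliberate choice to censor them. But the event is stated in full, and the next sentence names death for OS. As written, the rule is wrong for an endpoint of this name.

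**Conclusion.** The point holds. The stated definition is time to progression, and the planned Cox analysis would estimate the cause-specific hazard of progression while reporting it as PFS. That follows from the text alone.

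The size cannot be derived from the documents. The loss of 9% to 25% of events rests wholly on the assumed hazards and is illustrative. Whether the hazard ratio would be higher, lower or unchanged cannot be determined.

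Severity is moderate. PFS is one of several secondary endpoints; the primary endpoint (baseline global health status) and the sample size do not depend on it; deaths are fully counted in the separate OS analysis; and nothing is irrecoverable, because the necessary dates are collected. A reader might take this as a threat to the study's main conclusion; the documents give no ground for that.

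**What to change.** Before analysis, take one of two routes:

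- **Keep the name.** Define PFS as the time from diagnosis to the first of clinical or radiological progression (including recurrence) or death from any cause, with patients who have neither censored at their last clinical assessment.
- **Keep the event.** Rename the endpoint time to progression, treat death without progression as a competing event, and describe the Cox hazard ratio as cause-specific.

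Under either route, report the number of deaths without recorded progression by interval group, so that readers can see how far the two definitions diverge.

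The cost is one sentence in the analysis section. Time of death, recurrence and metastases are already on the CRF, so no new data are needed, and the sample size is unaffected.
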